
### Eligibility criteria

Eligible participants are (1) consenting US. military veterans who are ≥ 19 years of age; (2) currently unemployed or underemployed (i.e., working < 20 h/week in competitive employment, or currently employed in a job that is not meaningful or well-matched to the veteran); (3) desiring to work in a competitive job; and (4) have a history of current or lifetime OUD according to DSM-5. Veterans with a history of traumatic brain injury may be included as long as they do not have a severe cognitive disorder. The key to attaining and sustaining employment in the context of a recovery model is being recognized for the potential contributions one has made in the past and can once again address moving forward. Eligible veterans are either unemployed, marginally employed, or caught in the trap of working in entry level jobs unrelated to their past education, training and/or military experience. The absence of work or career choices with relevance or meaning to the veteran’s life can be a determinant of accepting and sustaining treatment adherence. Meaningful work is often described as employment in a valued environment or performing work tasks related to one’s personal preferences or life experiences, military or non-military.

Exclusion criteria include (1) a current diagnosis of schizophrenia, schizoaffective disorder or other psychotic disorders; (2) diagnosis of dementia or severe cognitive disorder; (3) presence of current severe and unstable medical condition or terminal illness, that would contraindicate study participation or expose them to an undue risk; (4) unlikely that participant can complete the study, e.g., expected deployment, incarceration, long-term hospitalization, or relocation from the vicinity; (5) active suicidal or homicidal ideation making it unsafe for the participant to be included; or (6) current participation in another vocational interventional trial.

### Recruitment procedures

Participants are recruited from the Tuscaloosa VA Medical Center and the Birmingham VA Health Care System as they naturalistically present for treatment in vocational rehabilitation services, residential treatment program, outpatient mental health clinics, and addiction recovery programs, are referred to the study, respond to the IRB-approved advertisement/letter, or make personal inquiry into the study. During the 3-year enrollment period, we plan for at least 180 veterans to be directly offered consent, 140 to sign consent, 120 to be randomized, and 100 veterans to complete the study at the two sites. Participants are modestly compensated for each baseline and the bimonthly assessment visits.

### Randomization and follow-up schedule

Participants who meet eligibility criteria are randomized (1:1) to either IPS or non-IPS-VR. Randomization uses a permuted block design of randomly varying block sizes stratified by site. Once assignment is made, the participant is analyzed in that group regardless of future events or services rendered, in accordance with the intent-to-treat principle.

Once informed consent is obtained, baseline assessments are administered. Participants are assessed at baseline and every 2 months (months 2, 4, 6, 8, 10, 12, 14, 16) and then final assessment at month 18 for employment outcomes and secondary outcomes. At each research visit, participants are assessed for the occurrence of adverse events or serious adverse events. The 18-month follow-up period allows for start-up time involved in each intervention prior to establishing competitive work and allows enough time for a participant to establish steady competitive work and achieve the secondary outcome goals.

### Clinical assessments

At baseline, the Clinical Research Coordinator (CRC) collects baseline demographics and characteristics, including age, gender, race, ethnicity, marital status, education level, military history (i.e., branch, period of service, combat exposure), status of housing and transportation, status of VA and non-VA disability, psychiatric treatment history, past and current treatment for OUD, and work history, including length of unemployment, type of previous job(s), and longest duration of competitive work. The Mini-International Neuropsychiatric Interview for DSM-5 is conducted by an investigator or CRC to confirm OUD diagnosis and document comorbidities [23]. Repeated measures include: the Patient Health Questionnaire-9 (PHQ-9) [24]; the Generalized Anxiety Disorder Scale (GAD-7) [25]; Brief Resilience Scale (BRS) [26]; Perceived stress Scale-10 (PSS-10) [27]; Quality of Life Scale (QOLS) [28]; Community Assessment Inventory (CAI) [29]; Alcohol Abstinence Self-Efficacy (modified for OUD) [30]; the Tobacco, Alcohol, Prescription Medications, and Other Substance (TAPS) Part-2 Tool [31]; and the Columbia Suicide Severity Rating Scale (C-SSRS) [32].

### Employment outcome assessments

The primary outcome is the number of weeks worked during the 18-months following randomization. A “week worked” is defined as working either full- or part-time in a competitive job during a 7-day period. Competitive employment is defined as a job that pays at least minimum wage based on wages, salary, or commission, is in a setting not set aside for those with mental illness or disabilities, and is not transitional work. The exploratory employment outcome will be ‘steady worker’ status, defined as obtaining competitive employment for at least 50% of the active follow-up period (i.e. ≥ 32 weeks). Longitudinal employment data will include number of weeks, days, and hours worked in a competitive job, dollars earned, type of job(s), number of jobs, and job satisfaction. Job satisfaction is measured with the Indiana Job Satisfaction Scale (IJSS) [33]. Employment outcomes and IPS or non-IPS-VR services received will be collected using a calendar approach and verified by copies of pay documents (e.g., pay stub, direct deposit notices, pay checks).

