### Overview of design, aims, and hypotheses

The purpose of this study is to evaluate the efficacy of IPS provided to veterans with OUD using a mixed methods approach. Our first aim is to conduct a prospective, multi-site, RCT to determine the efficacy of IPS compared to treatment-as-usual non-IPS vocational rehabilitation (non-IPS-VR). Consenting and eligible veterans who are currently unemployed or under-employed and are in treatment for OUD are randomized to either IPS or non-IPS-VR. Each participant receives IPS or non-IPS-VR and have outcomes assessed for 18 months. We hypothesize that participants who receive IPS will have significantly more weeks worked in a competitive job over 18 months compared to non-IPS-VR services. We also hypothesize that compared to non-IPS-VR, IPS recipients will earn significantly more income from competitive jobs and be significantly more likely to achieve steady employment, defined as working in a competitive job for 50% of the 18-month period. Our second aim is to explore and identify contextual barriers and facilitators of implementing rehabilitation services in both study arms and to achieving competitive employment among veterans with OUD. We will evaluate the implementation and employment challenges, optimal functioning, and OUD treatment adherence. We are employing a community-based participatory research (CBPR) approach to achieve this aim. True to CBPR approach, the interview guide for the present study was developed through an iterative interview process with various stakeholders, including employers of individuals with OUD, IPS and vocational rehabilitation specialists, Veterans, and researchers with expertise in this field. These various stakeholders were asked to identify various contextual barriers and facilitators of employment for Veterans with OUD. From these interviews, various overarching themes were developed to guide the development of the interview guide to further explore Veterans perspectives in the current study. The fundings of the barriers and facilitators will be published in a separate manuscript. For this study, we are also utilizing an iterative process of qualitative individual interviews with veterans with OUD that were randomized to IPS or non-IPS-VR. Our final aim is to evaluate the impact of IPS compared to non-IPS-VR on adherence to medications for OUD (MOUD) and rates of OUD relapse. We hypothesize that compared to non-IPS-VR, veterans who receive IPS will be significantly more likely to adhere to MOUD (i.e., those on MOUD only) and to have lower rates of OUD relapse.

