The primary hypothesis that participants randomized to IPS will work more weeks over the 18-months compared to those randomized to non-IPS-VR will be evaluated using predicted marginal means (i.e., LS-means) to estimate the difference in hours worked and test significance at the *p* < 0.05 level. Adhering to the principle of intent-to-treat, participants may discontinue the treatment intervention, but will be encouraged to remain in the study for outcome assessments for the 18-month follow-up period and will be analyzed as-randomized.

The exploratory employment outcome is the dichotomous classification of whether each participant is a ‘steady worker’ operationalized as a participant who holds a competitive job for at least 50% of the 18-month follow-up period. The analysis for this outcome will follow the same structure as for the primary employment outcome but using logistic rather than linear regression. Similar analyses for overall intervention effects will also consider outcomes of total time worked (days and hours), income earned from competitive sources, and the type and number of jobs held. These analyses will be descriptive and will be used to identify the overall time-trends of employment between the groups, including when the highest probability of employment is reached and whether the efficacy appears to decline after a period of time. This information can be used to further refine future IPS interventions to maximize the durability of intervention effects.

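### The steady-worker cut-off is given as 32 weeks, but half of the 18-month follow-up used elsewhere for the same outcome is about 39 weeks

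*Protocol article*

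**What the plan says.** The protocol article defines steady-worker status in three places.

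- **Overview of design, aims, and hypotheses:** steady employment is "defined as working in a competitive job for 50% of the 18-month period". The section hypothesizes that IPS recipients will be significantly more likely to reach it.
- **Employment outcome assessments:** the status is "obtaining competitive employment for at least 50% of the active follow-up period", which a parenthesis equates with 32 weeks or more. The word 'active' is not explained. The outcome is called exploratory.
- **Primary outcome analysis:** a steady worker is "a participant who holds a competitive job for at least 50% of the 18-month follow-up period". The outcome is again called exploratory, no week count is given, and its analysis is to follow the structure used for the primary outcome, with logistic regression.

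The length of follow-up is otherwise consistent. Employment outcomes says "The primary outcome is the number of weeks worked during the 18-months following randomization". The Randomization and follow-up schedule section has bimonthly visits to month 16, "then final assessment at month 18 for employment outcomes and secondary outcomes", and says that the 18 months leave room for start-up before competitive work begins. The Primary outcome analysis section scores a week with no employment data, including after early exit, as not worked.

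**The concern.** A proportion and a week count are presented as equivalent, and they are not equivalent for an 18-month follow-up. Two analysts could each follow the article faithfully, one using the week count and the other using half of 18 months, and code a different binary outcome for the same participant. Anyone with 32 to 38 weeks of competitive work changes class.

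At stake is the reported steady-worker rate in each arm and the comparison attached to one of the three employment hypotheses in the aims. The primary outcome is a count of weeks and does not use this cut-off. The sample size is based on a standardized difference in means and does not use it either.

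**Working it through.** **Inputs from the article.** Follow-up for employment: 18 months from randomization. Proportion: 50%. Unit: a 7-day week with any competitive work. Stated cut-off: 32 weeks.

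**Step 1: try to reproduce 32 weeks.** Cut-off = 0.5 × follow-up in weeks. The article gives no month-to-week conversion, so four were tried.

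| Convention | 18 months in weeks | Half |
|---|---|---|
| 52/12 weeks per month | 18 × 52/12 = 78.0 | 39.0 |
| 365.25/12 days per month | 18 × 365.25/12/7 = 78.3 | 39.1 |
| 30-day months | 18 × 30/7 = 77.1 | 38.6 |
| 28-day months | 18 × 4 = 72.0 | 36.0 |

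None gives 32. Even the shortest convention is 4 weeks above it.

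**Step 2: what 32 weeks represents.** 32/78 = 41% of follow-up. With 28-day months it is 32/72 = 44%.

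**Step 3: the window that 32 weeks would imply.** 32/0.5 = 64 weeks. In calendar terms, 64/(52/12) = 14.8 months; in four-week months, 64/4 = 16 months. The article defines no follow-up window of either length.

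**Step 4: who is affected.** The gap is 39 − 32 = 7 weeks. Totals of 32, 33, 34, 35, 36, 37 or 38 weeks are classified differently by the two rules.

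**Step 5: possible size (illustration only).** The article reports no employment outcomes, so the number of such participants cannot be derived from it. Simulated weekly employment histories were used under three assumed scenarios: median time to a job 14 to 60 weeks, weekly job loss 1.5% to 3%, and 15% to 40% never working. The steady-worker proportions were:

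| Scenario | Control, ≥32 / ≥39 weeks | IPS, ≥32 / ≥39 weeks | Arm difference, ≥32 / ≥39 weeks |
|---|---|---|---|
| 1 | 0.251 / 0.207 | 0.490 / 0.428 | 0.239 / 0.221 |
| 2 | 0.193 / 0.159 | 0.418 / 0.363 | 0.225 / 0.204 |
| 3 | 0.284 / 0.231 | 0.530 / 0.458 | 0.246 / 0.227 |

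The better arm was taken to be IPS. The share reclassified runs from 0.193 − 0.159 = 3.4% to 0.530 − 0.458 = 7.2% of an arm, or about 2 to 4 of 60. The arm difference shrinks by about 2 percentage points.

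**The case against.** The strongest defence is that 'active follow-up period' was meant as a window shorter than 18 months. Sixty-four weeks is 16 four-week months, and month 16 is the last bimonthly visit before the final one. That origin is possible but speculative. No such window is defined, the start-up time is placed inside the 18 months rather than subtracted from them, and the other two sections would still use the full 18 months. What stands is that the article does not show which number the authors intended.

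A second defence is that the aims and analysis sections agree with each other, so the outlier is one parenthesis and one undefined adjective, and an analysis plan that is not shown may settle the matter. This is fair, and it limits how far one can argue that the rule is open to choice after the data are seen. It does not make the stated number right.

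Two stronger readings are tempting, and the article does not support them.

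- **A third threshold based on each person's own observed time.** A reader might infer that someone who leaves at month 4 after working 9 of 17 weeks counts as steady. But the sentence that uses 'active' ties it to a fixed 32 weeks, which 9 weeks does not reach. Weeks after early exit are scored as not worked, and the steady-worker analysis follows the primary outcome's structure. The text carries two thresholds, not three.
- **That the discrepancy carries into a promised number needed to treat.** The Secondary outcomes analysis section promises effect sizes for primary and secondary outcomes. This outcome is labelled exploratory, so a number needed to treat for it is an inference.

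**Conclusion.** The point holds as an internal contradiction. Half of the stated 18-month follow-up is about 39 weeks, and 32 weeks is not half of any follow-up period that the article defines. This rests only on the article's own figures and does not depend on how months are converted to weeks.

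The severity is minor to moderate. The outcome is exploratory in two sections, although the aims attach a directional hypothesis to it, and the primary outcome and power are untouched. The likely effect is a few participants per arm and about 2 points on the arm difference. Those sizes depend wholly on assumed job-finding, job-loss and never-working rates, and should be read as an order of magnitude.

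**What to change.** Use one definition in the aims, Employment outcome assessments and Primary outcome analysis sections: a steady worker holds a competitive job in at least 39 of the 78 weeks after randomization. Use the same 78-week denominator for every participant, and score weeks without employment data as not worked, as is already done for the primary outcome. Delete the 32-week figure and the word 'active', and write 'at least' in all three places, since the aims section omits it.

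If 32 weeks or a shorter window is truly intended, either define that window with its start and end, or drop the 50% and state the week count alone (41% of 78 weeks). Then align the other two sections.

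The cost is a sentence of wording in each section, with no new data and no change to trial conduct. A 39-week rule can only lower the steady-worker rate in each arm, or leave it unchanged, relative to a 32-week rule. At publication 41 of the planned 120 participants had been randomized and no outcomes were reported. The change should be made and dated before outcomes are analysed.

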### MOUD outcome assessment

We are allowing Veterans on all types of MOUD (e.g., methadone, suboxone, naltrexone etc.) to be part of the study. We will ensure that type of MOUD will be controlled for in all statistical models at the end of the study. Adherence and relapse (i.e., opioid misuse ≥ 4 times/month) will be measured using the TAPS-2 Tool and pharmacy records. Adherence is defined as the number of days MOUD was received as indicated during the last 4 weeks of the intervention period.

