### MOUD analyses

An additional aim is to compare IPS to non-IPS-VR in terms of adherence to MOUD and relapse into heavy opiate use. We expect that MOUD adherence can be treated as a continuous variable in regression models. However, prior to modeling we will examine its distribution, to determine if this is appropriate. Relapse will be treated in two ways, as a binary indicator if any relapse as determined by TAPS (defined as opioid misuse ≥ 4 times/mo.), and the total number of self-reported days of misuse. The first dichotomous outcome will require logistic regression. The second approach will depend on the observed distribution and may be treated as either negative binomial or continuous. We will also explore the differences between groups in rates of relapse. The exploratory analysis will construct longitudinal models similar to those in our first aim considering outcomes of weekly adherence and relapse with that week’s employment status as well as lagged employment status (e.g., employment in previous weeks) as covariates to more directly examine the possible role of employment outcomes in explaining adherence and/or relapse. Further analyses may also include psychosocial covariates.

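### The MOUD adherence definition allows two scores for products not taken daily; if days of receipt are counted, the arm difference is diluted even after adjusting for MOUD type

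*Protocol article*

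**What the plan says.** Under MOUD outcome assessment, the protocol article sets a wide scope: "We are allowing Veterans on all types of MOUD (e.g., methadone, suboxone, naltrexone etc.) to be part of the study". The definition follows: "Adherence is defined as the number of days MOUD was received as indicated during the last 4 weeks of the intervention period". Adherence and relapse "will be measured using the TAPS-2 Tool and pharmacy records". The same section promises an adjustment: "We will ensure that type of MOUD will be controlled for in all statistical models at the end of the study".

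Under MOUD analyses, the plan for the scale is: "We expect that MOUD adherence can be treated as a continuous variable in regression models". This is conditional, because "prior to modeling we will examine its distribution, to determine if this is appropriate". That section also plans exploratory longitudinal models, "considering outcomes of weekly adherence and relapse with that week’s employment status as well as lagged employment status".

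The hypothesis, under Overview of design, aims, and hypotheses, is that IPS recipients will be "significantly more likely to adhere to MOUD (i.e., those on MOUD only" are considered). The article gives no formulation, dosing interval or product mix.

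**The concern.** The outcome is a count of days with no reference to how often the product is meant to be given. A count of this kind works when every participant takes a daily dose. It fails when some receive a product at longer intervals, because equal adherence then gives unequal scores and one point means different things for different people.

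The words *as indicated* may have been meant to deal with this, but they do not settle it. They can qualify the dose received on a given day, or they can mean that the day was covered by treatment as prescribed. Two analysts could score the same participant 1 or 28 from the same sentence.

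The estimate for the final aim is at stake: its size, and whether a difference in days can be interpreted at all. The weekly models inherit the problem. Under a receipt count, a fully adherent 4-weekly user shows receipt in only one week of four.

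**Working it through.** The article states no sample size, effect or power for MOUD adherence, so there is no figure of its own to reproduce.

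**Inputs**
- Window: 4 weeks = 28 days (MOUD outcome assessment).
- Size of the MOUD subset: 16 of 41 so far, 39.0%, split 12 IPS and 4 non-IPS-VR (Table 3). Applied to the target of 120: 120 × 16/41 = 46.8, about 47. The table row covers treatment in the 12 months before baseline, so it is only a rough guide to the number on MOUD in the final 4 weeks.
- Assumption: some participants use a product given once in 4 weeks. The share *s* is unknown and is varied from 0 to 50%.
- Assumption: true adherence is 70% in one arm and 85% in the other.

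**Scores under the two readings**

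| Participant | Days of receipt | Days covered |
|---|---|---|
| Daily product, fully adherent | 28 | 28 |
| Daily product, one dose missed | 27 | 27 (27/28 = 96.4%) |
| 4-weekly product, fully adherent | 1 | 28 |
| 4-weekly product, dose missed | 0 | as low as 0 |

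Under the receipt count, both kinds of missed dose cost 1 point. Under days covered they cost 1 and up to 28.

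**Expected arm difference under the receipt count**

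The true difference in adherence is 0.85 − 0.70 = 0.15. A daily user contributes 28 × 0.15 = 4.2 days and a 4-weekly user contributes 1 × 0.15 = 0.15. The average is (1 − s) × 4.2 + s × 0.15:
- s = 0: 4.20
- s = 10%: 3.78 + 0.015 = 3.80
- s = 25%: 3.15 + 0.0375 = 3.19
- s = 50%: 2.10 + 0.075 = 2.18

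**Simulation**

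There were 48 MOUD users, 24 per arm. Each participant's adherence was drawn from a beta distribution with mean 0.70 or 0.85 (parameters summing to 2). The analysis was a linear model tested at 5%, with 2,000 runs per row. The product term is an additive indicator for the 4-weekly product.

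| s | Difference, receipt count with product term | Difference, days covered with product term | Power, receipt count, no product term | Power, receipt count with product term | Power, days covered with product term |
|---|---|---|---|---|---|
| 0 | 4.2 | 4.2 | 55% | 55% | 55% |
| 10% | 3.9 | 4.2 | 31% | 51% | 49% |
| 25% | 3.2 | 4.2 | 18% | 44% | 42% |
| 50% | 2.1 | 4.2 | 9% | 32% | 34% |

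The product term recovers most of the power lost to the 1-versus-28 level shift. It does not recover the size of the difference: at s = 25% the estimate is about 3.2/4.2 = 76% of the days-covered difference, and at 50% it is half.

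**The case against.** **The wording.** Read as days on which the participant was receiving MOUD as prescribed, *as indicated* already means days covered, and a fully adherent 4-weekly user scores 28. This objection stands as far as it goes. A reader might infer that the plan certainly scores equally adherent people 1 and 28, but the text does not support that. It supports only that both scores are permitted.

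**The adjustment for MOUD type.** A reader might also infer that an uneven product mix will create a false treatment effect. With everyone fully adherent and 23 users per arm, 4 versus 8 on a 4-weekly product gives receipt-count means of (19 × 28 + 4)/23 = 23.3 and (15 × 28 + 8)/23 = 18.6, a gap of 4.7 days. That comparison is unadjusted and the mix is invented. With a product term that separates formulations, the gap is zero. The adjustment therefore answers the level shift on that condition. The article names drugs or products without formulation, so whether the condition is met is open. An additive term cannot repair the unequal weight of a missed dose.

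**The distribution check.** It would probably show a cluster at 1 and another at 28. It concerns the shape of the data, though, and does not say how such a cluster should be scored.

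**Derivation detail.** Rules for turning fills into days are commonly left to the full protocol or SAP, and their absence from an article is no fault. That stands. The point here is the stated definition, whose unit does not fit its stated scope. Nor does any text say that MOUD dispensed outside the pharmacy record is scored as zero, so no such error should be inferred.

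**Conclusion.** The definition is ambiguous for any product not taken daily, and one of its two readings gives a poor scale. Under that reading the arm difference is diluted even with a good adjustment for product: about 3.9, 3.2 and 2.1 days at assumed shares of 10%, 25% and 50% on a 4-weekly product, against about 4.2. If MOUD type does not separate formulations, the level shift stays as well and simulated power falls to 31%, 18% and 9%. At a share of zero this dilution and power loss do not arise.

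These sizes depend on the assumed product mix and the assumed 70% versus 85% adherence, neither of which comes from the article. The lasting harm is a diluted estimate that is hard to interpret. With an adequate product term, the power of the receipt count is close to that of days covered. The point concerns a final-aim outcome in a subset of participants; the primary outcome, weeks worked, and its power are not touched.

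**What to change.** Define adherence as the number of days covered by MOUD out of a fixed 28 days, for every participant in the as-randomized MOUD analysis set.

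- Count each fill or administration as covering its prescribed interval.
- Carry in supply from before the window. Otherwise a 30-day fill dispensed the day before the window opens shows no receipt date inside it, although it covers all 28 days.
- Score days after stopping MOUD as uncovered. A denominator of days prescribed would leave someone who stopped before the window with no score and would flatter someone who stopped partway. Stopping happens after randomization and may differ by arm, so the denominator should stay at 28.
- Adjust for formulation as well as drug.
- Use the same days-covered rule in the weekly adherence models.

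The cost is one reworded definition and a standard derivation from dispensing dates, days' supply and administration dates in records the study already uses. The small downside is that covered days are a proxy for days taken. The gain is an interpretable estimate rather than more power. Enrollment was still open and no outcomes were reported in the article, so the change can be made without reference to results.
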